## Abstract

**Background:**

The 5-Cog paradigm is a 5-minute brief cognitive assessment coupled with a clinical decision support tool designed to improve clinicians’ early detection of cognitive impairment, including dementia, in their diverse older primary care patients. The 5-Cog battery uses picture- and symbol-based assessments and a questionnaire. It is low cost, simple, minimizes literacy bias, and is culturally fair. The decision support component of the paradigm helps nudge appropriate care provider response to an abnormal 5-Cog battery.

**Objective:**

The objective of our study is to evaluate the effectiveness, implementation, and cost of the 5-Cog paradigm.

**Methods:**

We will enroll 6600 older patients with cognitive concerns from 22 primary care clinics in the Bronx, New York, and in multiple locations in Indiana for this hybrid type 1 effectiveness-implementation trial. We will analyze the effectiveness of the 5-Cog paradigm to increase the rate of new diagnoses of mild cognitive impairment syndrome or dementia using a pragmatic, cluster randomized clinical trial design. The secondary outcome is the ordering of new tests, treatments, and referrals for cognitive indications within 90 days after the study visit. The 5-Cog’s decision support component will be deployed as an electronic medical record feature. We will analyze the 5-Cog’s implementation process, context, and outcomes through the Consolidated Framework for Implementation Research using a mixed methods design (surveys and interviews). The study will also examine cost-effectiveness from societal and payer (Medicare) perspectives by estimating the cost per additional dementia diagnosis.

**Results:**

The study is funded by the National Institute of Neurological Disorders and Stroke of the National Institutes of Health (2U01NS105565). The protocol was approved by the Albert Einstein College of Medicine Institutional Review Board in September 2022. A validation study was completed to select cut scores for the 5-Cog battery. Among the 76 patients enrolled, the resulting clinical diagnoses were as follows: dementia in 32 (42%); mild cognitive impairment in 28 (37%); subjective cognitive concerns without objective cognitive impairment in 12 (16%); no cognitive diagnosis assigned in 2 (3%). The mean scores were Picture-Based Memory Impairment Screen 5.8 (SD 2.7), Symbol Match 27.2 (SD 18.2), and Subjective Motoric Cognitive Risk 2.4 (SD 1.7). The cut scores for an abnormal or positive result on the 5-Cog components were as follows: Picture-Based Memory Impairment Screen ≤6 (range 0-8), Symbol Match ≤25 (range 0-65), and Subjective Motoric Cognitive Risk >5 (range 0-7). As of December 2024, a total of 12 clinics had completed the onboarding processes, and 2369 patients had been enrolled.

**Conclusions:**

The findings of this study will facilitate the rapid adaptation and dissemination of this effective and practical clinical tool across diverse primary care clinical settings.

**Trial Registration:**

ClinicalTrials.gov NCT05515224; https://www.clinicaltrials.gov/study/NCT05515224

**International Registered Report Identifier (IRRID):**

DERR1-10.2196/60471

## Introduction

### Background and Rationale

#### Problem and Progress

Alzheimer disease and related dementias (ADRD) affect approximately 57 million people globally, a figure projected to rise to 152 million by 2050 [1,2]. Studies have long noted deficiencies and delays in individuals receiving a dementia diagnosis [3-12]. The World Health Organization’s Global Action Plan on Dementia includes a focus on the right to a timely dementia diagnosis to enable better planning, treatment, care, support, and quality of life [13]; for example, timely diagnosis can help individuals avoid preventable accidents and injuries leading to care escalation and can reduce distress for patients and caregivers [9,14-16]. In addition, several studies have estimated a potential cost saving of approximately US $10,000 per timely diagnosis because of delayed institutionalization, with the expectation that improved health and quality of life related to early diagnosis could result in even more cost savings [17].

Studies have repeatedly noted that delay and deficiency in diagnosis disproportionately impacts individuals from historically minoritized racial and ethnic groups as well as those from socioeconomically disadvantaged backgrounds [3-12]; for example, a recent nationally representative study found that a higher proportion of non-Hispanic Black and Hispanic individuals had a missed or delayed clinical dementia diagnosis compared to non-Hispanic White individuals (46% and 54% vs 41%; *P*<.001). This is thought to be an underestimate of the impact because the study relied on claims-based data, and non-Hispanic Black and Hispanic individuals may be less likely to access care that generates claims [18].

Experts recommend robust, multifaceted strategies to close these diagnosis gaps [15,17,19-24]; interventions must address implementation (“the actively planned process of putting evidence to use or integrating new interventions within a specific setting.” [25]) and dissemination (“the targeted distribution of information and intervention materials to a specific public health or clinical practice audience” [26]) challenges as much as they aim to achieve high clinical accuracy and quality [20,21,27-31]. The Consortium for Detecting Cognitive Impairment, Including Dementia, a collaborative research effort directed and funded by the National Institute of Neurological Disorders and Stroke and the National Institute on Aging of the National Institutes of Health (NIH), has produced promising paradigms to meet this need. As part of this effort, our team at the Albert Einstein College of Medicine and Montefiore Medical Center (hereinafter Montefiore Einstein clinics) in the Bronx, New York, United States, developed the 5-Cog paradigm [32,33]. In a randomized controlled trial (RCT) of 1200 older adults with cognitive concerns at an urban primary care clinic in a primarily Black and Hispanic community, we showed that the 5-Cog paradigm improves dementia care, most notably by increasing the rate of diagnosis of mild cognitive impairment (MCI) and dementia [33]. This detection and diagnosis increases opportunity for primary care providers (PCPs), patients, and patients’ families to intervene to potentially slow or prevent progression to dementia or, for individuals who do progress, to prepare in advance to meet the complex caregiving and clinical challenges to come [34].

Hence, our research questions for this cluster randomized trial were as follows:

Can a brief cognitive assessment paired with a clinical decision tree (5-Cog paradigm) increase the rate of new diagnoses of MCI syndrome or dementia in primary care patients presenting with cognitive concerns in real-world settings, across broad patient groups (hence its categorization as a pragmatic trial [35])?What are the determinants of the 5-Cog’s impact in these settings?

#### Updates to the 5-Cog Paradigm for This Trial

The 5-Cog paradigm (brief cognitive assessment battery and decision support tool) worked well in our initial trial. However, building on implementation reflections from that trial [27] as well as feedback from local primary care stakeholders, we have made 2 refinements to the 5-Cog paradigm to improve clinical utility and aid future dissemination. We substituted the gait speed measurement component of the 5-Cog with a questionnaire that assesses mobility and cognition. In addition, we modified the 5-Cog decision support component to capitalize on electronic medical record (EMR) capabilities and better align the 5-Cog paradigm with existing care provider workflows. All these modifications are described in detail in the following subsection (The 5-Cog Paradigm) and in the Interventions section.

#### The 5-Cog Paradigm

The 5-Cog paradigm is composed of a 5-minute brief cognitive assessment (the 5-Cog battery) combined with an EMR-embedded clinical decision support tool. The 5-Cog battery was granted US copyright registration effective December 14, 2023.

Clinical decision support provides timely information, usually at the point of care, to inform and improve decisions about a patient’s care [36].

The first of the 3 items in the 5-Cog battery is the Picture-Based Memory Impairment Screen (PMIS), created by Verghese et al [37], which uses 4 pictures to test free and cued recall after a delay of at least 2 minutes. Administration and scoring have been previously described [38]. This screener was selected because of ease of use (simple to administer after minimal training and does not require specialized technology), freedom from literacy bias (uses photographs of items instead of words), and cultural fairness (photographs were chosen and validated for consistent recognition by patients in the relevant cultural milieu). In our validation study, PMIS was shown to have high validity for distinguishing older adults with cognitive impairment from those without, regardless of age, sex, education, or presence of depression (sensitivity and specificity >90%) as well as excellent reliability (intraclass correlation 0.91) [37,38].

The second item in the 5-Cog battery is the Symbol Match [39], developed by one of our coinvestigators ([name]). It is an oral timed transcription task created to identify difficulties with divided attention, visual scanning, tracking, and motor speed. It requires individuals to quickly substitute (verbalize) numbers for an array of symbols using a key provided at the top of the page. After a practice run with 7 symbols, individuals are given 90 seconds to correctly name as many items as they can as quickly as they can without making a mistake. The number of correct oral substitutions at the end of 90 seconds is the participant’s score. Individuals who complete the task before the time limit receive a ceiling score of 65. Internal validation within our study population suggested 25 as the optimal cutoff score to identify cognitive impairment (refer to the Results section for details). The Symbol Match was chosen because of ease of use (requires no specialized equipment and minimal training to administer) [39]. The 90-second Symbol Match correlates highly with the established Symbol Digit Modalities Task [40,41], which can detect nonmemory impairments and functional changes [42]. This feature allows Symbol Match to detect patients with nonmemory impairments that may not be identified by the PMIS [39].

Finally, the 5-Cog incorporates an assessment of gait. The motoric cognitive risk (MCR) syndrome, first described by Verghese et al [43], and defined as slow gait in the presence of cognitive concerns, has been extensively validated to predict an elevated risk of dementia independent of other cognitive assessments [43-47]. Traditionally, the MCR syndrome assessment involves the measurement of gait speed. Given that gait speed is not routinely tested in current primary care environments and that it may present a barrier for 5-Cog implementation, we modified this assessment. For this study, we will be assessing the Subjective MCR (sMCR) screening tool, developed by Ayers et al [48], which uses the patient’s subjective reports of mobility and cognitive concerns via a 5-item questionnaire, rather than having a tester measure gait speed. Responses to these 5 questions are used to derive a weighted score that is used to define sMCR. Administration and scoring have been previously described [48]. We found the sMCR approach to have excellent discriminative validity versus objective MCR (defined using gait speed) and excellent predictive validity for incident dementia; in our validation study, participants who met the sMCR criteria had a >2-fold increased risk of developing dementia [48].

The 5-Cog paradigm’s EMR-based decision support tool includes 2 components: documentation of the patient’s 5-Cog battery result and recommended next steps that may be appropriate for further diagnosis or management of the patient’s cognitive concerns (clinical decision support). This “nudge” supports and supplements the provider’s own clinical decision–making process [49,50]. In this study, the decision support tool incorporates 3 additional features that make it resemble other EMR-based decision support systems: first, the 5-Cog result will be listed among other clinical practice advisories that contain information tailored to each patient regarding time-sensitive care needs. Second, providers will receive 5-Cog results through an interruptive alert when they access the patient’s chart (as they do in cases of other clinical issues that can impact patient safety). Finally, the decision support tool will include a direct link to orders for the next steps in care. This reduces clinician cognitive load by providing a menu of options (such as appropriate laboratory, imaging, and referral orders) and minimizes clicks by consolidating these options in one place.

Our 5-Cog 1.0 protocol [32] can be referenced for additional detail on the development and design of the 5-Cog paradigm. Figure 1 depicts the 2 components of the 5-Cog paradigm.

**Figure 1 figure1:**
[figure not shown]
(A) The 5-Cog battery (5-min cognitive assessment). (B) Decision support for a patient with a positive 5-Cog result. (C) Decision support for a patient with a negative 5-Cog result. EMR: electronic medical record.

#### Implementation Study

The United States Institute of Medicine (now the National Academy of Medicine) estimated a 17-year gap from when a clinical innovation is proven effective to when it is routinely implemented in clinical care [51]. Given that cognitive impairment detection paradigms are not adopted widely in primary care, it is important to systematically identify and address potential factors that influence implementation outcomes, that is, implementation determinants [52]. Our implementation measurements for the 5-Cog will be guided by the Consolidated Framework for Implementation Research (CFIR). The CFIR is an established implementation science theoretical framework for identifying implementation determinants [53,54]. We chose the CFIR because it facilitates the identification of implementation determinants that influence implementation outcomes either positively as facilitators or negatively as barriers [55-58]. Each CFIR construct is well defined, has established measures, and can be depicted in rich qualitative detail. The CFIR is practical because it is often used to both explore and subsequently optimize future implementation contexts and processes [59]. As with many implementation science frameworks, the CFIR does not mandate a specific data collection methodology [53]; studies applying the CFIR have used quantitative only, qualitative only, or mixed methods approaches [59]. We have chosen a mixed methods strategy to examine implementation contexts, processes, and outcomes. The study approach is based on the broader epistemology of critical realism [60] and more specifically the realist evaluation framework [61] wherein quantitatively measured implementation outcomes are explained by analyzing the relationships between implementation context and process factors. We will use the CFIR to identify implementation determinants through qualitative processes (interviews). We will use quantitative measures—the Acceptability of Intervention Measure (AIM), the Feasibility of Intervention Measure (FIM), and the Intervention Appropriateness Measure (IAM) [62]—to measure implementation outcomes. We will then analyze all findings using the CFIR as a lens to examine the relationships between these outcomes and implementation context and process factors [54,59].

#### Cost-Effectiveness Assessment

Currently, Medicare reimburses cognitive impairment assessments for older adults as part of their annual wellness visit (AWV) [22]. However, there is no standardized required form and output for this assessment. For health systems that would like to implement the 5-Cog for the AWV, questions may arise regarding its impact on costs. The 5-Cog battery is a low-cost intervention, requiring simple paper-and-pencil tools that are easily adapted to digital formats and minimal training to administer. For the 5-Cog decision support component, we anticipate programming and workflows to be translatable between EMR systems with a 1-time, upfront customization and without recurring software or staffing costs. Thus, the 5-Cog’s direct expenses predominantly include staffing costs (eg, salaries, benefits, and travel expenses for workers administering the 5-Cog). Given the short duration and minimal supplies cost of the 5-Cog, indirect expenses (eg, scheduling, record keeping, facility overhead, and equipment depreciation) and opportunity costs (eg, forgoing other billable care) are anticipated to be minimal. Investigators have previously reported costs associated with both community health workers (CHWs) and practice facilitators throughout Indiana and the Midwest in the United States [63]. There may also be costs associated with dementia care actions resulting from the use of the 5-Cog. However, these follow-up costs may be offset by cost savings resulting from earlier dementia care intervention [64].

The goal of our budget impact analysis (BIA) [65-67] and cost-effectiveness analysis (CEA) [68] is to understand the cost per cognitive case identified from a societal and payer (eg, Medicare) perspective to facilitate informed dissemination (per the CFIR model). The study design for estimating the financial effects involves addressing several issues, many predetermined by BIA and CEA best practices and the Consolidated Health Economic Evaluation Reporting Standards [65-68]. The BIA will determine financial planning and affordability, and the CEA will determine the effectiveness and value of the 5-Cog compared to enhanced usual care. The BIA can be used to determine financial adoption and scalability for national implementation.

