#### Participant Timeline

The 22 participating clinics were randomized in year 1 of the study. These clinics are onboarded in waves throughout the 5-year study period. The time period over which each clinic will experience active study recruitment (with the goal of enrolling 300 patients per clinic) is anticipated to vary from 3 to 12 months, depending on clinic size.

For individual patients in the effectiveness study, the initial screening and recruitment telephone call takes place within 1 week before a patient’s scheduled primary care visit and takes 10 to 15 minutes. Patients are then considered enrolled when they complete their scheduled PCP clinic appointment.

At the intervention clinics, participating patients are asked to arrive up to 1 hour early for their scheduled visit to allow sufficient time for undergoing the 5-Cog battery before meeting their care provider. The 5-minute assessment is completed at the clinic before the appointment.

In both intervention and control groups, patients remain enrolled for 90 days. Study outcomes are ascertained at 90 days (primary and secondary end points), at which point the enrolled patients are considered to have completed participation. This time window was selected because >95% of physician actions for dementia care were completed within this period in our initial trial [33].

Implementation study participants are enrolled when they consent to participate in a survey or an interview, and their enrollment is completed at its conclusion. Figure 2 depicts the study flow.

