#### Interventions for the Cost-Effectiveness Study

Billing and actuarial data will be extracted from the EMR for cost estimation. In parallel fashion to the intervention sites, costs are also collected at the control sites. Standardized cost calculators previously developed by investigators [67,84] will also be used to facilitate microcosting (measuring detailed resource use and unit costs to obtain precise estimates [85]) applicable to the 5-Cog paradigm. We will evaluate the cost of implementing and sustaining the 5-Cog paradigm by accounting for and itemizing specific program characteristics. We will evaluate differences in 5-Cog costs of care on the desired study outcomes compared to enhanced usual care.

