#### Cost-Effectiveness Outcomes

The cost calculator includes parametric models of cost inputs; cost model outcomes from this study will thus allow scenario analyses [67,84]. The proposed calculator will incorporate both the direct costs of the intervention (test administration, staffing costs, etc) and costs associated with interventions prompted by the 5-Cog (brain imaging, specialist referral, laboratory tests, etc). The cost calculator will thus enable others to determine 5-Cog delivery costs and implementation specifics such as the cost of hiring at future implementation sites. Data collected for the BIA will determine financial planning and affordability, while data collected for the CEA will determine the effectiveness and value of the 5-Cog paradigm compared to enhanced usual care.

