#### CEA and Economic Impact

Using data from the BIA cost-tracking tool, the cost-effectiveness ratio [109,110] “numerator” will account for site personnel and other costs at both intervention and control sites. The denominator will represent the number of cognitive impairment cases identified at the 5-Cog and control sites. In summary, the cost-effectiveness ratio represents the incremental cost of the 5-Cog intervention compared to enhanced usual care to achieve a clinically meaningful change, divided by the difference in effectiveness, to determine the cost per cognitive impairment case identified. This is expressed as follows:

Cost-effectiveness ratio = intervention costs + Δ (health care costs) / Δ health outcomes (5-Cog) – Δ health outcomes (enhanced usual care comparison group)

To assess uncertainty in our analysis, we will follow the recommendations of the International Society for Pharmacoeconomics and Outcomes Research and the Society for Medical Decision Making Modeling Good Research Practices Task Force [63,65-68,111]. Variability of inputs across study sites with differing levels of social determinants of health will be included in analyses [112]. Differences in intervention and health care costs due to secondary procedures will be assessed individually using negative binomial regression and reported with a 95% CI. Only statistically significant differences from the regression analyses will be incorporated into the cost-effectiveness ratio. Differences in health outcomes will be assessed as described in the Effectiveness Study: Statistical Plan subsection, and the estimate of the GLME model, if significant, will be incorporated into the cost-effectiveness ratio. Costs will be discounted at a 3% annual rate for the trial period, as recommended by the Second Panel on Cost-Effectiveness in Health and Medicine [113].

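### The cost-effectiveness ratio is called societal, but its printed cost terms are only intervention and health care costs, so as written it is a health care sector ratio that omits patient time

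*Protocol article*

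**What the plan says.** The Abstract (Methods) promises "cost-effectiveness from societal and payer (Medicare) perspectives by estimating the cost per additional dementia diagnosis". The Cost-Effectiveness Assessment section repeats the two perspectives: the goal is "to understand the cost per cognitive case identified from a societal and payer (eg, Medicare) perspective".

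CEA and Economic Impact then gives one formula. It begins "Cost-effectiveness ratio = intervention costs + Δ (health care costs) / Δ health outcomes (5-Cog" and subtracts the outcome under enhanced usual care in the denominator. In words, the numerator "will account for site personnel and other costs at both intervention and control sites". There is no second formula for the second perspective.

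The inputs are described in three other places:
- Interventions for the Cost-Effectiveness Study: "Billing and actuarial data will be extracted from the EMR for cost estimation", supplemented by microcosting of the program.
- Cost-Effectiveness Outcomes: the calculator covers "direct costs of the intervention (test administration, staffing costs, etc) and costs associated with interventions prompted by the 5-Cog", with imaging, specialist referral and laboratory tests as the examples of the latter.
- Cost-Effectiveness Assessment: staff pay, benefits and travel, overhead, and an opportunity cost whose one example is billing that the provider forgoes.

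Participant Timeline states that at intervention clinics "participating patients are asked to arrive up to 1 hour early for their scheduled visit". The article describes no such request at control clinics.

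**The concern.** A societal perspective differs from a payer or health care sector one in who bears the costs that are counted. It takes in resources given up outside the health system, of which patient and caregiver time is the obvious one here. The article claims that perspective twice, but the rule it prints for the ratio has no place for such costs.

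This goes beyond an unlisted item, because the stated rule does not match the stated perspective. It also concerns a cost that differs by arm. The early arrival is part of delivering the 5-Cog, so it does not cancel in the comparison with enhanced usual care. Additional tests and referrals would also take up patient time.

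Cost-effectiveness is one of the three trial aims, and the ratio is meant to inform dissemination of a paradigm described as low cost. A health system or policy reader who sees the label societal would assume that burden on patients had been counted.

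**Working it through.** **Step 1. Compare the perspective with the costs named.** The article states no cost per case, so there is no cost figure to reproduce. Sorting every cost item it names by who bears it:

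| Section | Items named | Borne by |
|---|---|---|
| Cost-Effectiveness Assessment | staff pay, benefits and travel; EMR customization; overhead; forgone billing; follow-up care | provider, program, payer |
| Interventions for the Cost-Effectiveness Study | billing and actuarial data; program microcosting | provider, program, payer |
| Cost-Effectiveness Outcomes | test administration, staffing; imaging, referral, laboratory tests | provider, program, payer |
| CEA and Economic Impact | site personnel and other site costs; intervention costs; change in health care costs | provider, program, payer |

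Patient time, caregiver time, patient travel and informal care appear in no row. Data Collection Methods adds nothing: its two sources are EMR data and feedback, and the patient feedback concerns perceptions and experiences. The stated limitation of the economic analysis is its short time horizon, not its cost scope.

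**Step 2. Check the effect inputs.** Statistical Plan inputs: 14% versus 2%, intraclass correlation 0.05, 300 patients per clinic, 6600 patients allocated 1:1 by clinic, so about 3300 per arm.
- Design effect: 1 + 299 × 0.05 = 15.95.
- Effective size per arm: 3300 / 15.95 = 206.9.
- Power for 14% versus 2%: 99.5%, which agrees with the article's figure of more than 99%.

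**Step 3. Patient-hours left out per additional diagnosis.** Assume every enrolled intervention patient is assessed.
- Patients assessed per additional diagnosis: 1 / (0.14 − 0.02) = 8.33.
- Additional diagnoses in the arm: 3300 × 0.12 = 396.
- Omitted hours per additional diagnosis: (extra minutes / 60) / 0.12.

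The article bounds the extra time at both ends: 5 minutes for the test alone, 1 hour as the ceiling on early arrival. The hourly value is not in the article; US $10 to $40 is an assumption.

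| Extra time per patient | Hours per additional diagnosis | At $10/h | At $40/h |
|---|---|---|---|
| 5 min | 0.69 | $7 | $28 |
| 15 min | 2.08 | $21 | $83 |
| 30 min | 4.17 | $42 | $167 |
| 60 min | 8.33 | $83 | $333 |

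If the true difference were half as large (6 points, an assumption), the 1-hour figure would double to 16.7 hours, or $167 to $667.

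**Step 4. Direction for this item.** Early arrival adds to the incremental numerator and leaves the denominator unchanged. For this item alone, the ratio as written understates the incremental cost. The screening call is made in both arms and is not counted.

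**The case against.** The strongest reply is that this is a condensed article. Itemising costs by perspective commonly belongs in a full protocol or economic plan, and the article points to best-practice guidance, reporting standards and detailed microcosting. The formula is introduced as a summary, the numerator in words includes unspecified other costs, and the calculator's lists are open-ended. Nothing expressly excludes patient time.

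Part of this stands: a fuller plan may contain the missing term, and the fix may amount to printing it. But the open-ended wording supplies no patient-borne cost. The other costs are placed at the sites, every example belongs to the provider, program or payer, and the printed formula has no term into which patient time would fall. What the cited guidance requires cannot be checked here.

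Three stronger readings are tempting, and the document does not support them:
- A reader might infer that the societal cost per case is too low overall. The Introduction cites a potential saving of about US $10,000 per timely diagnosis from delayed institutionalization, and Cost-Effectiveness Assessment says follow-up costs may be offset by savings. A 90-day follow-up would largely miss such savings. The net sign of everything omitted is unknown.
- A reader might infer that patient time rivals the delivery cost that is counted. The article gives no staff minutes or wages, and delivery also includes benefits, travel and EMR customization. That comparison would rest on assumptions on both sides.
- A reader might infer that the societal and payer results would coincide. The article does not say how they are to differ. They could differ even with the listed items, for example if a Medicare ratio leaves out staffing that Medicare does not reimburse.

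**Conclusion.** The point holds as a mismatch between the claimed perspective and the printed ratio. Followed as written, the result labelled societal is a health care sector ratio, and it leaves out a patient burden that the protocol itself places on the intervention arm only.

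In hours, the omission is between about 0.7 and 8.3 patient-hours per additional diagnosis. This rests on the article's own 14% versus 2% and on every intervention patient being assessed. One hour is a ceiling, so the upper figure is a bound and not an estimate. The dollar range in the table depends entirely on the assumed hourly value and may be modest beside the full numerator. No claim is made about the net bias of a complete societal ratio.

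The consequence is confined to the third aim. The primary outcome, the power and the effectiveness analysis are unaffected.

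**What to change.** Choose one of two changes before the economic analysis is run:

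1. **Keep the societal perspective.** In CEA and Economic Impact, print a separate societal numerator that adds patient time and accompanying caregiver time to the two existing terms. Base the time on visit arrival and 5-Cog administration times, include time for the tests and referrals prompted where it can be estimated, apply a standard hourly value, and give a sensitivity range. State which items enter the payer ratio, so that the two perspectives are distinguishable.
2. **Narrow the claim.** Remove the word societal from the Abstract and from Cost-Effectiveness Assessment, and call this a health care sector and payer analysis.

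The first option costs one additional cost line and some recording of times, and it makes the societal ratio slightly less favourable. The second costs only a narrower stated perspective. Neither touches enrolment or the effectiveness outcomes.
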